#### Combination therapy group (CT)

The combination therapy group included the same education and drug as the DT, along with 10 sessions of physical therapy.

*Physical therapy*: patients will receive 2 courses of physical therapy, including 10 sessions of ultrashort wave therapy (Shantou Medical Equipment Factory Co., Ltd., China) and LIPUS (Shenzhen Dongdixin Technology Co., Ltd., China). Ultrashort wave therapy takes 20 min for each knee joint, and the treatment intensity is based on the patient's feelings, that is, there is a feeling of warmth during treatment. LIPUS takes 5 min for each knee joint, and the treatment intensity is 1.4 W/cm^2^. All treatments will be performed by two trained physiotherapists to ensure therapeutic efficacy.

During the trial, patients’ condition is aggravated, and they can be allowed to use relevant drugs for treatment. However, any medication use will be recorded in the medical record and diary.

### Outcome measures

Outcome measures will be measured according to Osteoarthritis Research Society International [31]. Baseline measurements will be performed in the first stage, and the second stage will be measured at baseline and 5 (T5) and 10 (T10) days after intervention. The timeline for the second stage is shown in Table 1.

**Table 1 Tab1:**
[figure not shown]
The participant timeline in
the second stage

### Primary outcomes:

(1) The difference in knee pain before and after treatment, will be measured by the NRS, a standard tool for the study of chronic pain, that is an 11-number scale from 0 to 10, with 0 being no pain and 10 being severe pain. The minimum clinically important difference (MICD) is 1.8 [32, 33].(2) Association of pain severity with task-activated fNIRS. Data collection: The NirSmart portable near-infrared functional brain imaging system (Danyang Huichuang Medical Equipment Co., Ltd., China) will collect the cerebral cortical activity of the participants in the 30-s chair-stand test, the timed up-and-go test, the 40-m fast-paced walk test and the stair-climb test (9 steps) [34]. The test will be carried out in a quiet corridor and stairwell. Before each test, the test procedure will be explained to the participants, and the participants will be informed that if there is no special situation to keep quiet during the test, the test will be started after the participants fully understand. At the beginning of each test, the participants will need to stand quietly for 10 s to obtain the resting state fNIRS, and then the corresponding test will be carried out according to the rules. Forty effective test channels consisting of 24 light transmitters and 16 light receivers cover the functional areas of the whole brain. Changes in blood oxygen will be measured at two wavelengths (760 and 850 nm) with a sampling frequency of 10 Hz.

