**Discussion:**

By analyzing the fNIRS data of healthy volunteers and KOA patients, our study will be determined whether fNIRS can be used as a new indicator to reflect the severity of pain in KOA patients. Subsequently, the same fNIRS data for KOA patients before and after the intervention will be collected to provide an accurate evaluation criterion for the effect of physical therapy on KOA.

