### Secondary outcomes

(1) The Western Ontario and McMaster Universities Osteoarthritis Index (WOMAC) will be used to assess knee pain, stiffness and physical function. The WOMAC is a self-assessed health status scale for patients with KOA consisting of 24 items in three subscales of pain (5 items), stiffness (2 items), and physical function (17 items). All items are scored from 0 (asymptomatic) to 4 (very severe), and the total score ranges from 0 to 96, with higher scores indicating more severe symptoms [35, 36]. The test–retest reliability of the scale is 0.83, and the validity is 0.77 [37]. The study showed an MICD of 12% improvement from the baseline on this scale [38].(2) The pain catastrophizing scale (PCS) is a self-assessment scale used to assess the degree of exaggerated negativity in response to persistent and anticipatory pain, with a total score of 0–52; higher scores indicate more severe pain catastrophically [39].(3) Association of pain severity with task-state functional connectivity fNIRS. Data collection: firstly, we need to obtain the functional connectivity fNIRS in the resting state, the participants need to sit on the chair on the side of the quiet corridor, and face the wall to keep quiet and calm breathing. In this resting state, the participants wear the instrument and keep it for 5 min. Secondly, we need to obtain the task-state functional connectivity fNIRS. The participants stand up from the chair and breathe calmly for 30 s. After getting the initial instructions, the participants perform a 6-min walking test in a quiet corridor [34]. Before the start of the whole test, the test process will be explained and answered by the participants. Participants need to be quiet throughout the test.

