## Statistical analysis

Data analysis will use an intention-to-treat analysis strategy. Data analyses will use SPSS (26.0). P ≤ 0.05 will be significantly different. The raw data collected by fNIRS will be preprocessed by NIRSPARK software, including artifact processing, filtering, segmentation and baseline comparison. At the same time, the fNIRS data will be analyzed using the statistical analysis module of MATLAB (R2020a). Component comparability of baseline data between the two groups will be performed using the chi-square test and independent samples t test. The frequency and percentage of count data will be calculated in the statistical description; the data of measurement data following a normal distribution will be described by the mean ± standard deviation. For the comparison between groups after the intervention, the independent samples t test will be used if the data follow a normal distribution, and the Mann‒Whitney U rank sum test will be used if the data are nonnormally distributed. For intragroup comparisons before and after the intervention, a paired t test will be used if the data follow a normal distribution, and the Wilcoxon rank sum test will be used for data that are not normally distributed.

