## Conclusion

KOA is a chronic degenerative joint disease that causes joint pain and dysfunction. The main objective of KOA treatment is to reduce pain and improve dysfunction, in which physical factor treatment is an important intervention [40]. In this study, changes in cerebral cortical blood flow measured by fNIRS were used to evaluate changes in brain activation status in normal subjects and KOA patients and the consistency with the severity of pain in KOA patients. In addition, we will evaluate the effect of physical factor therapy on pain and dysfunction in KOA patients based on fNIRS.

The study will be conducted in the Rehabilitation Medical Center of West China Hospital of Sichuan University, and patients will be enrolled through poster recruitment and outpatient registration. This study is a noninvasive, adaptive and innovative way to evaluate the effectiveness of physical therapy in KOA patients.

FNIRS is an innovative neuroimaging technique for measuring hemodynamic changes during brain activation [41]. fNIRS has the characteristics of portability, wireless nature and lightweight, which can be used as an objective index to evaluate changes in pain [42]. A recent study used fNIRS to evaluate the effect of exercise on the severity of pain, and the results showed that there was a significant difference in the activation of the prefrontal cortex before and after exercise [22]. However, there is currently no study comparing changes in cerebral hemodynamics between healthy subjects and KOA patients and whether changes in cerebral hemodynamics are used as objective indicators of pain and functional improvement in KOA patients.

Therefore, the advantages of this study are mainly summarized as follows: (1) On the basis of previous studies, healthy subjects were added to evaluate the degree of cerebral cortex activation in healthy subjects; (2) evaluating the changes in cerebral blood flow between KOA patients with different pain severities and to provide an experimental basis for fNIRS as an objective index for the clinical pain evaluation of KOA patients; and (3) After using physical factors to treat KOA patients, we compared the changes in cerebral blood flow, NRS, and functional activity scores between different groups of KOA patients under different action instructions.

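### The fNIRS outcomes are defined as associations with pain severity, but the named tests estimate no association, and a healthy-versus-KOA difference would not supply one

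*Protocol article*

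**What the plan says.** Under Primary outcomes, item (2) of the protocol article is "Association of pain severity with task-activated fNIRS". Under Secondary outcomes, item (3) is "Association of pain severity with task-state functional connectivity fNIRS". Neither item says which scale measures severity. The pain scale in primary item (1) is the NRS, "an 11-number scale from 0 to 10, with 0 being no pain and 10 being severe pain".

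The Statistical analysis section names its tests by situation:
- Baseline comparability: chi-square and independent-samples t.
- Between arms: "For the comparison between groups after the intervention, the independent samples t test will be used if the data follow a normal distribution", otherwise Mann-Whitney.
- Within arms: "For intragroup comparisons before and after the intervention, a paired t test will be used if the data follow a normal distribution", otherwise Wilcoxon.
- fNIRS: "the fNIRS data will be analyzed using the statistical analysis module of MATLAB (R2020a"), with no test or model attached.

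On what will be concluded, the Discussion part of the abstract says: "By analyzing the fNIRS data of healthy volunteers and KOA patients, our study will be determined whether fNIRS can be used as a new indicator" of how severe the pain of KOA patients is. The Methods section describes stage 1 as a baseline comparison of those two groups. The Conclusion section adds an aim confined to patients, "evaluating the changes in cerebral blood flow between KOA patients with different pain severities", and speaks of consistency between fNIRS and pain severity in KOA. It gives no test, model or cut-points for either.

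**The concern.** The section that lists the tests has one for every kind of comparison in the trial except the quantity that defines a primary and a secondary outcome. An association is a feature of a sample of paired values. A t test, a rank test or a before-after test on the fNIRS signal answers a different question.

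The abstract's inference makes this more than a missing detail. A case-control difference says that people with KOA differ from people without it. They may differ in cortical response for reasons unrelated to how much pain each patient has. Whether fNIRS can serve as a pain-severity measure, and then as a yardstick for physical therapy in stage 2, depends on the relation among patients.

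**Working it through.** **Matching outcomes to tests**

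| Outcome or aim | Quantity needed | Named test that estimates it |
|---|---|---|
| NRS, WOMAC, PCS | difference between arms or over time | t, Mann-Whitney, paired t, Wilcoxon |
| Healthy versus KOA, stage 1 | difference between groups | independent t |
| Primary (2), secondary (3) | association of fNIRS with pain severity | none |
| Patients with different severities (Conclusion) | relation of fNIRS to severity within KOA | none |

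**Plan's own figures.** No figure is given for the association. The Sample size section rests on NRS alone: 30 per group at 90% power and 0.05, 72 after the dropout allowance, and 72/3 = 24 healthy volunteers. The 30 cannot be recomputed because no effect size or SD is stated.

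**Does a group difference imply tracking among patients?** Inputs from the article: 24 healthy, 72 KOA, entry NRS of at least 3, threshold 0.05. Assumptions, not in the article: two-sided tests; fNIRS signal with SD 1; patient NRS centred on 5.5 with SD 1.5, rounded and held within 3 to 10; group shift of 0, 0.5 or 0.8 SD. There were 4,000 simulated trials per row.

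| Group shift | True r among KOA patients | Healthy-vs-KOA t test significant | KOA-only correlation significant |
|---|---|---|---|
| 0.5 SD | 0 | 55% | 5.1% |
| 0.8 SD | 0 | 92% | 5.5% |
| 0 | 0.4 | 4.5% | 93% |
| 0.8 SD | 0.4 | 92% | 92% |

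Hand check of the 92%: the noncentrality is 0.8 × √(24 × 72/96) = 0.8 × √18 = 3.39, and Φ(3.39 − 1.96) = Φ(1.43) = 0.92.

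The group test responds only to the shift and the KOA-only correlation only to r. Neither stands in for the other, whatever values are assumed.

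**Can the planned patients support the right analysis?** Fisher z, two-sided 0.05, one fNIRS measure: power = Φ(atanh(r) × √(n − 3) − 1.96), with √(72 − 3) = 8.307.
- r = 0.37: 0.388 × 8.307 = 3.23; Φ(1.27) = 0.90.
- r = 0.30: 0.310 × 8.307 = 2.57; Φ(0.61) = 0.73.
- r = 0.20: 39%. r = 0.40: 94%.

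Smallest r with 90% power = tanh((1.960 + 1.282)/√(n − 3)): 0.37 for n = 72 and 0.40 for n = 60.

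These figures need a single prespecified measure. The article describes four tasks and 40 channels. With Bonferroni correction, the smallest r with 90% power at n = 72 rises to 0.43 for 4 tests and 0.53 for 4 × 40 = 160.

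**The case against.** A reader might infer that the plan cannot show that fNIRS tracks severity, and that its severity claim rests only on the healthy contrast. The documents do not support either reading.
- The Conclusion section states a comparison among KOA patients by severity, and a consistency aim. The abstract's sentence is condensed: it says that data of both groups will be analysed, not that a group difference will count as proof.
- NRS and fNIRS are both scheduled in the same patients at baseline, T5 and T10, so the data for a KOA-only analysis will exist.
- The MATLAB analysis is unspecified, not limited to group tests. The paired t and Wilcoxon tests are before-after tests, so it would be wrong to call every named test a two-group comparison.
- The arm comparison that the article describes is of patient-level values such as change in cerebral blood flow, to which the named tests do apply.

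A reader might also picture a correlation pooled over all 96 people, which would be inflated by the group contrast. No section proposes one, so it is no evidence about this plan.

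Finally, this is a condensed article whose full analysis plan may exist. Choice of model and covariates could properly sit there.

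All of this stands, and it narrows the point. It does not remove it. The article does not defer the analysis: it lists specific tests, and the list leaves out the quantity that defines a primary outcome. The link that the abstract makes between the two-group data and severity would also need rewording whatever a later plan specifies.

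**Conclusion.** The point holds in this form: the named tests do not estimate primary outcome (2) or secondary outcome (3), and a healthy-versus-KOA difference would establish discrimination, not tracking of severity among patients. The design is adequate; the stated analysis and the abstract's inference are what need correcting.

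The logic does not depend on any assumed value. The simulated percentages do: they rest on the assumed group shift and NRS distribution. The power figures rest on two-sided testing, one prespecified fNIRS measure and 72 patients with usable data. The randomised NRS comparison, which is the other primary outcome and the basis of the sample size, is unaffected.

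**What to change.** In the Statistical analysis section:
1. State that the association is estimated in the KOA patients only, and that NRS is the pain-severity scale.
2. At baseline, use Spearman correlation or regression of one prespecified fNIRS measure on NRS. This is a relation between patients.
3. In stage 2, use a repeated-measures model relating change in fNIRS to change in NRS at T5 and T10, adjusted for arm. This asks whether signal and pain move together within a patient, and should be reported separately from the baseline result.
4. Treat secondary outcome (3) in the same way with its connectivity measure.
5. Keep healthy versus KOA as a separate discrimination question.

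In the abstract, reword the Discussion so that the severity claim rests on the KOA-only analysis.

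The cost is wording and the choice of one fNIRS measure before the data are analysed. It needs no added patients, visits or equipment. The downside is scientific: the severity claim may come out weaker than the group difference would suggest, and an r near 0.2 would probably be missed (39% power).

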### Secondary outcomes

(1) The Western Ontario and McMaster Universities Osteoarthritis Index (WOMAC) will be used to assess knee pain, stiffness and physical function. The WOMAC is a self-assessed health status scale for patients with KOA consisting of 24 items in three subscales of pain (5 items), stiffness (2 items), and physical function (17 items). All items are scored from 0 (asymptomatic) to 4 (very severe), and the total score ranges from 0 to 96, with higher scores indicating more severe symptoms [35, 36]. The test–retest reliability of the scale is 0.83, and the validity is 0.77 [37]. The study showed an MICD of 12% improvement from the baseline on this scale [38].(2) The pain catastrophizing scale (PCS) is a self-assessment scale used to assess the degree of exaggerated negativity in response to persistent and anticipatory pain, with a total score of 0–52; higher scores indicate more severe pain catastrophically [39].(3) Association of pain severity with task-state functional connectivity fNIRS. Data collection: firstly, we need to obtain the functional connectivity fNIRS in the resting state, the participants need to sit on the chair on the side of the quiet corridor, and face the wall to keep quiet and calm breathing. In this resting state, the participants wear the instrument and keep it for 5 min. Secondly, we need to obtain the task-state functional connectivity fNIRS. The participants stand up from the chair and breathe calmly for 30 s. After getting the initial instructions, the participants perform a 6-min walking test in a quiet corridor [34]. Before the start of the whole test, the test process will be explained and answered by the participants. Participants need to be quiet throughout the test.

### Sample size

The sample size will be determined by comparing the NRS scores before and after treatment based on a preliminary study of the first 10 participants. With a yielding power of 90% and a significance level of 0.05, using G*Power (3.1.9.4) software, the sample size is intended to consist of 30 participants in each group. With a 20% dropout rate, the two groups required 72 participants. KOA patients and healthy volunteers will be calculated in a ratio of 3:1, for a total of 24 healthy volunteers.

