### Randomization

After the baseline measurement, the computer software SPSS (26.0) will be used to generate a random number table, and patients will be assigned to the CT or the DT in a ratio of 1:1 by a simple random method. Write the random number assigned to each group on a piece of paper and place it in an opaque envelope. Envelopes will be randomly assigned to participants by the independent individual not involved in the study.

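### The 90% power and 30 per group rest on a before-after NRS comparison, so they are not supported as the power of the randomised CT-versus-DT comparison

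*Protocol article*

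**What the plan says.** The protocol article's Sample size section gives one basis for the calculation: "The sample size will be determined by comparing the NRS scores before and after treatment based on a preliminary study of the first 10 participants". It continues "With a yielding power of 90% and a significance level of 0.05, using G*Power (3.1.9.4) software", and concludes that "the sample size is intended to consist of 30 participants in each group". It then adds an allowance for loss: "With a 20% dropout rate, the two groups required 72 participants". The section gives no CT-DT difference, SD, standardised effect, sidedness or type of test.

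Other sections describe the randomised comparison. The opening of Methods calls the second stage a parallel randomised controlled trial, and under Randomization "patients will be assigned to the CT or the DT in a ratio of 1:1 by a simple random method". Under Interventions, CT is the DT package of education and drugs plus physical therapy. Statistical analysis provides for the between-arm contrast: "For the comparison between groups after the intervention, the independent samples t test will be used if the data follow a normal distribution", with a Mann-Whitney test otherwise. It lists the paired before-after test separately, as a within-group analysis.

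The first primary outcome is worded as a change: "The difference in knee pain before and after treatment, will be measured by the NRS". The same item adds: "The minimum clinically important difference (MICD) is 1.8". The Sample size section does not refer to that figure.

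**The concern.** A sample size has to be justified for the contrast that answers the trial's question. Here that contrast is CT minus DT, because only the difference between arms isolates the physical therapy. A change from before to after treatment also contains whatever the shared drugs and education do. It may contain regression to the mean as well, since patients enter only with an NRS score of at least 3. Both arms share these components, and they cancel in CT minus DT. The size of a before-after change therefore says little about the size of the between-arm difference.

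The stated power is the yardstick by which a non-significant result will be read. If 90% belongs to the before-after change, a null CT-DT result could be taken as good evidence that physical therapy adds nothing when the trial had a much smaller chance of detecting a benefit. The planning effect also appears to have been read off 10 people, which is a weak basis for an effect size on either reading.

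**Working it through.** **Inputs from the protocol article.** Power 90%, significance level 0.05, 30 per group, 20% dropout and 72 in total (Sample size); 1:1 allocation (Randomization); 1.8 points on the NRS (Primary outcomes). Sidedness is not stated; two-sided is assumed unless noted.

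**Can 30 per group be reproduced?** No, because no effect size, SD or test is given. One can only solve backwards for the standardised effect that gives 90% power, using the non-central t distribution.

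- Paired test: df = n − 1, non-centrality = dz × √n. With n = 30, 90% power needs dz = 0.612 (one-sided: 0.547).
- Two-sample test: df = 2n − 2, non-centrality = d × √(n/2). With n = 30 per arm, 90% power needs d = 0.851 (one-sided: 0.765).

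**The total.** 60 × 1.20 = 72, so the printed total follows from 30 per group. After 20% loss, 72 × 0.80 = 57.6 patients remain, about 29 per arm.

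**If the calculation was paired.** Put the implied effect into the between-arm test with 30 per arm, in SD-of-change units. At full size, the non-centrality is 0.612 × √15 = 2.37, against 0.612 × √30 = 3.35 in the paired test.

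| CT-DT difference as a share of the before-after effect | d | Power, 30 per arm | n per arm for 90% |
|---|---|---|---|
| 100% (DT does not change) | 0.612 | 64.5% | 58 |
| 75% (DT achieves a quarter of CT's change) | 0.459 | 42% | 101 |
| 50% (DT achieves half of CT's change) | 0.306 | 21% | 226 |

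With a one-sided test, the first row becomes 67% at d = 0.547. The shares are illustrative scenarios; the document gives no expected change for DT.

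**If the calculation was two-sample.** It needs d = 0.851. With 1.8 points as the between-arm target (an assumption), the SD may be at most 1.8 / 0.851 = 2.11. The SDs below are also assumed, since the document gives none.

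| Assumed SD | d = 1.8 / SD | Power, 30 per arm | Power, 29 per arm | n per arm for 90% |
|---|---|---|---|---|
| 2.0 | 0.90 | 93% | 92% | 27 |
| 2.5 | 0.72 | 78% | 77% | 42 |
| 3.0 | 0.60 | 63% | 61% | 60 |

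The 29-per-arm column uses the same two-sample formula with n = 29.

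**The case against.** The strongest reply is that the calculation may have been two-sample all along. A figure per group is the natural output of a two-sample routine, whereas a paired routine returns a number of pairs. The primary outcome is itself worded as a before-after difference, so the sentence about comparing scores before and after treatment may only name a change score that was then compared between arms. A difference of 1.8 with an SD of 2.1 gives exactly 30 per group. On that reading, what is missing is the effect size, SD and test name, and an article may leave such detail to the full protocol.

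Much of this stands. It rules out the stronger inference that the trial is underpowered: the 65%, 42% and 21% figures hold only on the paired reading, and the last two also rest on assumed DT responses. It does not remove the point, because the section does state a basis, and that basis is before versus after rather than CT versus DT.

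Three further inferences are tempting but unsupported:

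- **A before-after change is always larger and less variable than a between-arm difference.** Its variability depends on the before-after correlation, which is not given; with equal variances, the SD of change is below the SD of a single score only if the correlation exceeds 0.5.
- **The 10 pilot participants are analysed again in the trial.** The wording about the first 10 could suggest it, but the section calls this a preliminary study and does not say whether they count among the 72.
- **The 1.8 points should have been the between-arm target.** The article attaches that figure to the NRS outcome, which it words as a before-after difference. Using it between arms needs its own justification.

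**Conclusion.** The point holds as a defect in the stated justification. The only basis given for the 90% is a before-after comparison, while the randomised question is CT minus DT, so the claim is not supported as the power of that comparison. The true power is undetermined. At two-sided 0.05 with 30 per arm, it is about 65% or less if a paired effect of 0.61 SD was carried over. It is 90% if the calculation was two-sample and the true standardised difference is 0.85. The conclusion that the basis is mismatched rests on the text alone; the size of any shortfall rests on the unnamed test, the assumed SDs and the DT response. The matter is worth correcting before results are read against the 90%, but it does not show that the number of patients is wrong.

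**What to change.** Rewrite the Sample size section for the CT-DT difference in NRS, saying whether this is the change score or the day-10 score. State:

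- the target difference (1.8 points is one candidate, to be justified as a between-arm target);
- the SD and its source;
- the sidedness and the test used in G*Power.

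Use the 10 preliminary participants to inform the SD rather than the effect size, and say whether they count among the 72. Then report the power that 72 randomised patients deliver after 20% dropout, over a range of SDs, as in the second table above.

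The cost is one paragraph. No increase in N, change of endpoint or change of test is needed. The downside is that the stated power may become less favourable.

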### Interventions

In the first stage, 24 healthy volunteers and 72 KOA patients will not receive any treatment, with only one baseline data measurement. In the second stage, 72 patients with KOA will be randomly divided into two groups: the drug therapy group (DT) and the combination therapy group (CT).

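### The 20% dropout allowance multiplies 60 by 1.2 to reach 72; keeping 30 per group after 20% loss needs 75 randomised, or 76 for equal arms

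*Protocol article*

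**What the plan says.** The Sample size section bases its calculation on "comparing the NRS scores before and after treatment based on a preliminary study of the first 10 participants". It gives the design values as "With a yielding power of 90% and a significance level of 0.05, using G*Power (3.1.9.4) software", and the result is that "the sample size is intended to consist of 30 participants in each group". The allowance for losses follows: "With a 20% dropout rate, the two groups required 72 participants".

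The total of 72 is then used throughout. The Abstract and the Participants section repeat it, and the Interventions section says that "72 patients with KOA will be randomly divided into two groups". The control sample depends on it as well: "KOA patients and healthy volunteers will be calculated in a ratio of 3:1, for a total of 24 healthy volunteers". The Randomization section sets 1:1 allocation. No section defines dropout in another way or gives a separate reason for 72.

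**The concern.** The section gives three figures: 30 per group needed, 20% dropout expected, and 72 randomised. They do not fit together. The total looks as if 20% was added to the required 60, whereas a dropout rate is taken off the number randomised. If dropout runs at exactly the planned rate, the trial finishes with fewer patients than the same section says it needs, and the 90% power is no longer supported by the plan's own assumptions.

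**Working it through.** **Inputs, all from the Sample size section unless noted**

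- Required per group: 30, so 60 in total
- Dropout rate: 20%
- Total randomised: 72, or 36 per group under 1:1 allocation (Randomization section)
- Power 90%, significance level 0.05, sidedness not stated
- Effect size and standard deviation: not given

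**Step 1: reproduce the stated total.** Required number × (1 + dropout) = 60 × 1.20 = 72. Per group, 30 × 1.20 = 36. This matches exactly.

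**Step 2: apply the rate to those randomised.** Required number / (1 − dropout) = 60 / 0.80 = 75. Per group, 30 / 0.80 = 37.5, which rounds up to 38, so equal arms need 76.

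**Step 3: see what 72 delivers at 20% loss.** 72 × 0.80 = 57.6 patients, or 36 × 0.80 = 28.8 per group. The shortfall against 60 is 2.4 patients.

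**Step 4: find the dropout that 72 can absorb.** 1 − 60/72 = 0.167, or 16.7%.

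**Step 5: effect on power.** The 30 per group cannot be re-derived without an effect size, so the standardised effect d has to be assumed. I back-solved it from 30 per group with the non-central t distribution (two-sample, two-sided, significance level 0.05). There are two bounds:

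- *Lower:* 30 per group gives exactly 90%, so d = 0.851.
- *Upper:* 30 is the smallest whole number reaching 90%, so d is just under the value at which 29 per group would reach it, 0.866.

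| Completers per group | Power, d = 0.851 | Power, d = 0.866 |
|---|---|---|
| 30 and 30 | 90.0% | 91.0% |
| 28.8 and 28.8 | 88.8% | 89.8% |
| 29 and 28 | 88.4% | 89.5% |

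The result hardly depends on the choice of test. With d set so that 30 gives exactly 90%, 28.8 gives 88.9% for a one-sided two-sample test and 88.7% for a paired before-after test.

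**The case against.** The strongest reply is that this is a wording slip of little consequence: 2.4 completers and about one percentage point of power, with no change to design, enrolment or analysis. The size is conceded. What remains is that the printed figures contradict each other, and a fuller document could not reconcile them, since 72 × 0.80 is not 60.

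A second reply is that the Statistical analysis section specifies intention-to-treat, so all 72 might be analysed and nothing would be lost. The article does not say how the outcomes of patients who leave would be obtained. The Sample size section inflates for dropout, so it already counts those patients as lost. The intention-to-treat statement therefore does not remove the shortfall, but the power figures above do assume that only completers contribute.

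A third reply concerns the power figures themselves, and it stands in part. The effect is back-solved, and neither the test nor its sidedness is stated, so a range is more honest than one value. If 30 had been rounded up from a smaller computed number, power at 28.8 might still reach 90%, but the article gives 30 as the result and mentions no such rounding.

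Finally, allocation is "patients will be assigned to the CT or the DT in a ratio of 1:1 by a simple random method", so the arms need not be 36 and 36. If each patient is assigned independently, the standard deviation of one arm's size is √(72 × 0.25) = 4.2 patients, more than the shortfall. The 29-and-28 split is therefore an illustration, not a forecast. Imbalance provides no offset, because for a fixed total and equal variances it lowers power.

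**Conclusion.** The concern holds. The total of 72 comes from multiplying by 1.2 and does not provide for 20% dropout. It is 3 patients short of the 75 needed, or 4 short of the 76 needed for equal arms, and it covers a loss of 16.7%. This part is pure arithmetic on the article's own numbers and rests on no assumption.

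The loss of power is minor: about 89% in place of 90%, with a range of 88.8% to 89.8% at 28.8 per group. That rests on a two-sided two-sample t test, on 30 being the smallest group size that reaches 90%, and on an analysis of completers. The trial is not compromised, but its sample-size statement is wrong as written and should be corrected.

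**What to change.** Correct one sentence in the Sample size section in one of these ways:

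1. Keep 72 and state that it allows for 16.7% dropout from the required 60.
2. Keep 72 and the 20% rate, and state that about 57 evaluable patients (28 to 29 per group) are then expected, with power of about 89% on the assumption that 30 per group gives 90%.

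Both leave enrolment unchanged, and 72 / 3 = 24 healthy volunteers still follows. The only cost is a slightly less favourable statement.

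If the sponsor prefers to keep both 20% dropout and 90% power, the number randomised becomes 75, or 76 for equal arms. The 3:1 ratio then gives 75 / 3 = 25 volunteers, or 76 / 3 = 25.3, rounded up to 26. The total of 72 would have to change wherever it appears: Abstract, Participants, Interventions and Sample size.
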